### Outcomes

The study will be conducted over a period of 1 year (48 weeks) and will include a treatment period of 3 months (12 weeks) and an observation period of 9 months (36 weeks). In all, one primary outcome indicator, one secondary outcome indicator, and four security indexes will be analyzed:
Primary outcome indicator: 24-h urinary protein quantity.

Any change in total urine protein level at 24 h will be assumed to directly reflect a therapeutic effect; hence, this clinical laboratory index should be recorded every 2 weeks during the treatment period and every 4 weeks during the follow-up period (17 times in total). In addition, creatinine excretion measured vs expected for gender will be detected at the same time to verify the adequacy of 24-h urine collection indirectly.

Total urine protein at 24 h is the most important outcome. In previous studies, we found that the improvement of urinary protein of TG at week 4 and week 8 was better than that of the control group, while the difference at week 12 was not significant. Based on these subtypes, this study will further explore the difference in treatment between the two groups. Therefore, we will set 17 nodes, including the treatment period and the follow-up period, to compare the differences in urine protein between the two groups at each node, rather than only retaining the last result at 48 weeks.
2)Secondary outcome indicator: red blood cells in urine.

Compared to the primary indicator, the urine red blood cell count is considered secondary because urine red blood cells recede more slowly than protein recedes. This clinical laboratory index should be recorded at the same points during treatment and follow-up as the primary outcome indicator (17 times in total).
3)Security indexes.
Blood system: the white blood cell count (WBC) and platelet count (PLT).In patients taking immunosuppressors or prednisone, there is a potential risk of abnormalities in the blood system in terms of leukocyte and platelet counts. Blood tests were performed to determine the leukocyte count 17 times during and after treatment, as already described.Liver and kidney function test: glutamate alanine transferase (ALT), glutamate aspartate transferase (AST), serum creatinine (Scr), and blood urea nitrogen (BUN) levels should be monitored.In patients using any drug, there is a potential risk of dysfunction in the liver and kidney. Because they are the main indicators used to evaluate liver and kidney function damage, blood should be drawn from the vein to perform ALT/AST and Scr/BUN tests 11 times during and after treatment.

Time frame for testing: week 0 (before treatment)/week 1/week 2/week 4/week 8/week 12 of the treatment phase and week 20/week 28/week 36/week 44/week 48 of the follow-up phase.

### Randomization

Participants will be randomized at a 2:1 ratio by the Central Randomization System of the China Academy of Chinese Medical Science, which is an online, central randomized service. Allocation concealment will be ensured, as the service will not release the randomization code until the patient has been recruited into the trial, which takes place after all baseline measurements have been completed.

The study participants are stratified by disease subtype. Both heavy type and light type will be included in each subcenter. The trained clinicians divide those children with HSPN who met the requirements into light type and heavy type according to the amount of urine protein within 24 h. After signing the informed consent, clinicians will log into the central random system according to their account password, and then click “random” under the corresponding subtype to conduct random grouping.

### Allocation

All drugs will be uniformly distributed to the subcenters by the First Affiliated Hospital of Henan University of TCM. Each drug is obtained from the same manufacturer with the same specifications according to the following details:
Tripterygium glycoside tablets (Jiangsu Meitong Pharmaceutical Co. Ltd; SFDA approval number Z33020422, 10 mg).Sulfotanshinone sodium injection (Shanghai First Biochemical Pharmaceutical Co. Ltd; SFDA approval number H31022558, 2 ml, 10 mg).Qingrezhixue granules (hospital preparations created by [name] and produced at the First Affiliated Hospital of Henan University of TCM; Patent No. 201810118156.8).Prednisone acetate tablets (Zhejiang Xianju Pharmaceutical Co. Ltd; SFDA approval number H33021207, 5 mg).Benazepril hydrochloride tablets (Beijing Nuohua Pharmaceutical Co. Ltd; SFDA approval number H20000292, 10 mg).Low molecular weight heparin calcium injection (Tianjin Hongri Pharmaceutical Co. Ltd; SFDA approval number H20020470, 6000 U).Dipyridamole tablets (Linfen Qilin Pharmaceutical Co. Ltd; SFDA approval number H14020538, 25 mg).Chinese medicine granule and granule simulation drugs (placebo) (produced by Jiangyin Tianjiang Pharmaceutical Co. Ltd).

All manufacturers meet GMP (Good Manufacturing Practice) standards. All drugs should be kept in a dry and cool place by a specially trained person.

### Blinding

Because TCM syndrome differentiation is needed during the research process, this is an open-label trial. To improve patient compliance in patients who come to the Chinese Medicine Hospital for TCM treatment, a regular group will be treated with Chinese medicine granule simulation drugs (placebo).

### Sample size calculation

The previous clinical results showed that the clinical control rate of proteinuria was 48.6% in the TCM group and 35.7% in the western medicine group during the 4th week of treatment. Based on these results, in this study, the total sample size was calculated as 405 cases if the TCM group and the western group were included at a ratio of 2:1. The δ value between them is expected to be 15% with a significance level of α = 0.05 and an assurance of 1 – β = 90%. We will increase the sample size by approximately 20% to reach 500 cases in consideration of the possibility that some patients could miss visits due to the long illness course and follow-up time. Clinical experience indicate that heavy patients will account for approximately 25% of eligible individuals; hence, 120 patients with heavy HSPN and 380 patients with light HSPN will be included.

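### The 405 patients at 90% power imply an undeclared one-sided 5% test and a 15-point difference, larger than the 12.9 points cited; two-sided, power is about 82–83% and 70–71%

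*Protocol article*

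**What the plan says.** The Sample size calculation section starts from earlier trial results: "the clinical control rate of proteinuria was 48.6% in the TCM group and 35.7% in the western medicine group during the 4th week of treatment". It presents the calculation as resting on those results. Its planning difference is another number, however: "The δ value between them is expected to be 15" per cent. The other inputs are "a significance level of α = 0.05" and "an assurance of 1 – β = 90" per cent. The result is that "the total sample size was calculated as 405 cases if the TCM group and the western group were included at a ratio of 2:1", raised by about 20% to 500 to allow for missed visits. The allocation ratio agrees with the Randomization section: "Participants will be randomized at a 2:1 ratio".

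The section does not say whether α is one-sided or two-sided. It does not name a formula, and it gives no reason for planning on 15 points. The Statistical analysis section refers to showing a difference by logistic regression and names a Cox model and Fisher's test, again without a direction.

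**The concern.** The published inputs do not fit together in two respects. First, the cited rates differ by 48.6 − 35.7 = 12.9 points, while the calculation uses 15. Second, a reader who takes α = 0.05 in the usual two-sided sense cannot reach 405 at 90% power for either difference.

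What is at stake is how the result will be read. The Outcomes section reports that in earlier work the week-12 difference was not significant, so a null finding is a real possibility. A reader told that the trial had 90% power will give a null finding more weight than it deserves if the true power is nearer 70% or 80% for the difference the plan itself cites.

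**Working it through.** **Inputs**, all from the Sample size calculation section: control rate p_C = 0.357; TCM rate p_T = 0.507 (control plus 15 points) or 0.486 (as cited); allocation 2:1; α = 0.05; power 90%. Sidedness is not stated, so both cases are computed.

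**Formulas**, with d = p_T − p_C and total = 3 × n_C:

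- Unpooled: n_C = (z_α + z_β)² × [p_C(1 − p_C) + p_T(1 − p_T)/2] / d²
- Pooled: n_C = {z_α √[1.5 p̄(1 − p̄)] + z_β √[p_C(1 − p_C) + p_T(1 − p_T)/2]}² / d², where p̄ = (p_C + 2p_T)/3

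**Step 1: reproduce 405.** For 35.7% versus 50.7% the variance term is 0.2296 + 0.2500/2 = 0.3545, and d² = 0.0225. At one-sided 5% and 90% power, (1.645 + 1.282)² = 8.564. So n_C = 8.564 × 0.3545 / 0.0225 = 134.9 and the total is 404.8. Rounded up, that is 135 + 270 = 405, an exact match.

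**Step 2: the same inputs, two-sided.** (1.960 + 1.282)² = 10.507, so n_C = 10.507 × 0.3545 / 0.0225 = 165.6 and the total is 496.7.

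**Step 3: all combinations at 90% power** (totals before rounding up)

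| Rates | One-sided 5%, unpooled / pooled | Two-sided 5%, unpooled / pooled |
|---|---|---|
| 35.7% vs 50.7% (15 points) | 404.8 / 416.1 | 496.7 / 511.6 |
| 33.6% vs 48.6% (15 points, anchored on the TCM rate) | 397.4 / 410.7 | 487.6 / 505.1 |
| 35.7% vs 48.6% (12.9 points) | 547.2 / 560.8 | 671.4 / 689.3 |

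At the stated 90% power and with the cited rates, every total near 405 is one-sided with 15 points. Other near matches need a stated input to change. For example, 12.9 points at one-sided 5% gives 395 to 407, but at 80% power. A non-inferiority calculation with a 15-point margin and both rates at 35.7% gives 396, but that is also one-sided 5%, and the text does not describe non-inferiority.

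**Step 4: power delivered.** Unpooled power is Φ(d/SE − z_α), where SE = √[p_C(1 − p_C)/n_C + p_T(1 − p_T)/n_T].

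- 15 points, 270:135: SE = 0.05125 and d/SE = 2.927. One-sided, Φ(2.927 − 1.645) = 90.0%; two-sided, Φ(2.927 − 1.960) = 83.3%.
- 12.9 points, 270:135: SE = 0.05124 and d/SE = 2.518. One-sided, Φ(2.518 − 1.645) = 80.9%; two-sided, Φ(2.518 − 1.960) = 71.1%.

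The pooled version uses the pooled standard error at the critical value. Taking 500 as 333:167:

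| Difference | Evaluable | One-sided 5%, unpooled / pooled | Two-sided 5%, unpooled / pooled |
|---|---|---|---|
| 15 points | 405 | 90.0% / 89.3% | 83.3% / 82.1% |
| 15 points | 500 | 94.6% / 94.2% | 90.2% / 89.4% |
| 12.9 points | 405 | 80.9% / 79.9% | 71.1% / 69.7% |
| 12.9 points | 500 | 87.6% / 86.8% | 79.9% / 78.7% |

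**The case against.** The strongest reply is that no arithmetic error has been shown. The inputs give 405 exactly at one-sided 5%, the article never says two-sided, and a condensed article may leave sidedness to the full protocol or analysis plan. This stands in part. A reader might infer that the stated 90% is simply wrong. The documents do not support that, because 90% is correct for 15 points if a one-sided 5% test was meant. What remains is that the article publishes a complete set of numbers, and those numbers hold together only under a condition it does not state.

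A second reply is that a planning difference need not equal an earlier estimate, particularly since the regimen changed: the Background describes Xiangdan injection in the earlier study, and the Intervention section now uses tanshinone IIa. That is fair. Choosing 15 points is not an error in itself. However, the text presents the calculation as based on the cited rates and does not explain the extra 2.1 points.

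A third reply is that 405 is the pessimistic case. The cited rates are from week 4, whereas the 20% allowance covers visits missed over 48 weeks, so more than 405 may be evaluable at week 4. As an assumption, 450 evaluable would give 86–87% two-sided power for 15 points. With all 500 analysed, the unpooled figure is 90.2%. A reader might therefore infer too much from the 405 figures alone if they conclude that 90% is out of reach under any two-sided test. That full-enrolment case does not rescue the 12.9-point difference, where two-sided power is still only 79–80%.

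**Conclusion.** The point holds, conditionally on sidedness. The 405 reproduces at the stated 90% power and cited rates only under a one-sided 5% test that the article does not declare, combined with a difference larger than the one it cites.

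If α is two-sided, which is the usual reading but an assumption here, the 405 evaluable patients fall short of 90% for 15 points by about 7 to 8 percentage points of power. They would miss a true 12.9-point difference about 29–30% of the time. With all 500 analysed, the 15-point shortfall practically disappears, and the chance of missing 12.9 points is 20–21%. If α is one-sided, the 90% stands for 15 points but not for 12.9.

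The one conclusion that depends on neither sidedness nor formula is that 90% power is not delivered for 12.9 points, whether 405 or 500 patients are analysed. All figures use the normal approximation for two independent proportions at 2:1; the choice between unpooled and pooled moves them by about 1.5 percentage points at most.

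**What to change.** Rewrite the paragraph in the Sample size calculation section so that it:

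- states that 405 rests on a one-sided 5% calculation for 35.7% versus 50.7%;
- says openly that the planned 15 points exceeds the cited 12.9 points, with the reason if there is one;
- gives two-sided 5% power for both differences at 405 and at 500, using one named formula throughout. Unpooled, these are 83.3% and 71.1% at 405, and 90.2% and 79.9% at 500. Pooled, they are 82.1% and 69.7%, and 89.4% and 78.7%.

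State the sidedness of the tests in writing before the results are read. If they are two-sided, these figures must replace the 90%. If they are one-sided, the 90% may stay for 15 points, with the 80–81% for 12.9 points (87–88% with all 500) beside it.

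No further enrolment is proposed; the Trial status section puts the trial at the stage of statistical work on the data. The cost is one paragraph and a stated power that looks less favourable.

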### Data collection and management

Case report forms (CRFs), medical reports and laboratory test reports will make up the main data source file for the subjects in this clinical trial. Data obtained from each subcenter should be regularly transferred in a timely manner to the subject undertaking unit. For all eligible CRFs, two data entry staff will independently input the contents into the database as double copies according to the requirements. During this process, if any data are in doubt, they will be entered into a “Data query table” and fed back to the clinical researchers by the data administrators. The database is locked and will be submitted to the quality control group of the “Twelfth Five-year” Plan for the National Science and Technology Program through the data management network after a data consistency check, all database modifications, and a data quality audit are completed.

### Statistical analysis

All statistical analyses in the study will be carried out by a third party, the Chinese Academy of Traditional Chinese Medicine, using SAS version 6.12, which is validated software for clinical studies. Logistic regression is used to show a difference in the prevalence of clinical control/remission in both groups, including age, gender, place of residence, parents’ educational background, and so on. For the outcome “time from positive to negative for urinary protein and urinary occult blood”, a Cox proportional hazards model is used. The incidence is described for adverse events and Fisher’s test will be used for comparison. Besides, groups and time of therapy on curative effect will be considered. If there are interaction effects between groups, simple effect analysis is performed; if not, grouping effect/time of therapy on curative effect should be considered separately.

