Diagnostic criteria	2 main symptoms of blood heat (or 1 main symptom + 2 secondary symptoms) + 1 main symptom of blood stasis

**Table 3 Tab3:** Observation protocol to be followed during treatment and follow-up

Observed indicator/week		Treatment stage (week)								Follow-up stage (week)								
		0	1	2	4	6	8	10	12	16	20	24	28	32	36	40	44	48
Main	24-h urinary protein quantity	×	×	×	×	×	×	×	×	×	×	×	×	×	×	×	×	×
Secondary	Urine red blood cells	×	×	×	×	×	×	×	×	×	×	×	×	×	×	×	×	×
Security	Routine blood tests	×	×	×	×	×	×	×	×	×	×	×	×	×	×	×	×	×
	Hepatic and renal function	×	×	×	×		×		×		×		×		×		×	×

2.Follow-up stage (12–48 weeks).

The 12-week treatment stage will be followed by a 36-week follow-up stage. The main aim of the follow-up is to monitor a series of laboratory indicators and determine the disease recurrence rate. The details are presented in Table 2.

In patients who meet the clinical control standards after 12 weeks of treatment, medication will be stopped and the patients will begin follow-up. The clinical control standards mean that RBC counts and 24-h protein in urine are at normal levels, and urine routine examinations are negative for protein and occult blood. For those patients who do not meet the clinical control standards by 12 weeks, other treatment options could be appropriately selected in the professional judgment of the clinicians. The clinicians who are evaluating the follow-up laboratory results (and determining whether there is a relapse or whether the patient has reached clinical control standards) are not blinded to the patient’s treatment assignment. The criteria for efficacy evaluation are presented in Table 4.

**Table 4 Tab4:** Criteria for efficacy evaluation

Primary outcome	Clinical control rate	Significant efficiency	Effective rate	Ineffective rate
PRO in urine	Negative	PRO decreased by 2+	PRO decreased by +	PRO decreased less than +
	24-h urinary protein quantity is normal	24-h urinary protein quantity reduced > 50%	24-h urinary protein quantity reduced between 30 and 50%	24-h urinary protein quantity reduced < 30% or no change
RBC in urine	U-OB: negative	U-OB: RBC reduction ≥ ++/HP	U-OB: RBC reduction ≥ +/HP	U-OB: no improvement or aggravation in RBC
	RBC ≤ 5/HP	RBC count decreased By > 50%	RBC count decreased between 30 and 50%	RBC count decreased < 30% or no change
Total therapeutic effect	Meet all these requirements	Meet all these requirements	Meet all these requirements	Meet all these requirements

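### No named analysis tests the declared primary outcome, 24-h urinary protein quantity, on its own scale, and the sample size rests on yet another version of it

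*Protocol article*

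**What the plan says.** The Outcomes section names one primary outcome: "Primary outcome indicator: 24-h urinary protein quantity". It sets 17 measurement points "to compare the differences in urine protein between the two groups at each node" and says that this is preferred to keeping only the week-48 result.

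The Statistical analysis section names these analyses:

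- A logistic model: "Logistic regression is used to show a difference in the prevalence of clinical control/remission in both groups".
- A Cox model for the outcome "time from positive to negative for urinary protein and urinary occult blood".
- A sentence with no model attached: "groups and time of therapy on curative effect will be considered", with simple effects if there is an interaction.
- Fisher's test for adverse events.

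Table 4 (Intervention section) grades efficacy in bands. The top grade requires that "24-h urinary protein quantity is normal" and that urine protein is negative. Lower grades are set by the percentage reduction, and the total effect also brings in the red-cell criteria.

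The Sample size calculation starts from earlier results: "clinical control rate of proteinuria was 48.6% in the TCM group and 35.7% in the western medicine group during the 4th week of treatment". It assumes a 15-point difference.

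**The concern.** A primary outcome needs an analysis that tests it. Here the quantity is declared, while the models with a name are fitted to a yes/no state and to a time to conversion. Three versions of the main efficacy variable are in play: the protein quantity over 17 visits, clinical control or remission at an unstated time, and control of proteinuria at week 4. A reader cannot tell which result decides the trial.

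The choice of scale also matters. In the logistic model, a child whose protein falls a long way but stays above normal counts the same as a child with no change. At the cited week-4 rates, 51.4% of the TCM arm (100 − 48.6) and 64.3% of the control arm (100 − 35.7) fall in that undivided group. The Outcomes section itself treats any change in 24-h protein as reflecting treatment effect.

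**Working it through.** **1. Match each variable to its analysis.**

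| Variable | Where | Named analysis |
|---|---|---|
| 24-h protein quantity, 17 visits | Outcomes (primary) | None |
| Clinical control/remission | Statistical analysis | Logistic |
| Time to negative protein and occult blood | Statistical analysis | Cox |
| Curative effect by group and time | Statistical analysis | No model named |
| Control of proteinuria, week 4 | Sample size calculation | Two proportions |

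The follow-up text under Intervention defines the clinical control standards by red cells as well as protein. The logistic outcome may therefore differ even from the sample-size outcome.

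**2. Reproduce the plan's sample size.** Inputs: control rate 0.357, difference 0.15 (so 0.507), power 90%, ratio 2:1.

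N = 3 × [pC(1−pC) + pT(1−pT)/2] × ((z_α + z_β)/δ)²

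- The bracket is 0.2296 + 0.1250 = 0.3545.
- One-sided 5%: 3 × 0.3545 × ((1.645 + 1.282)/0.15)² = 405, the stated figure.
- Two-sided 5%: 3 × 0.3545 × ((1.960 + 1.282)/0.15)² = 497.

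The article does not state sidedness, so both are carried below. The 405 children split 270:135.

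**3. Power of the binary comparison.** Power = Φ(δ/SE − z_α), with SE = √(pT(1−pT)/270 + pC(1−pC)/135).

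- 48.6% vs 35.7%: SE 0.0512, power 71% two-sided and 81% one-sided.
- 50.7% vs 35.7%: SE 0.0512, power 83% two-sided and 90% one-sided.

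**4. Full scale, assuming a uniform normal shift.** If control is a cut on a normal variable (for example log protein), the shift is d = Φ⁻¹(pT) − Φ⁻¹(pC).

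- 48.6% vs 35.7%: d = −0.035 + 0.366 = 0.331 SD.
- 50.7% vs 35.7%: d = 0.018 + 0.366 = 0.384 SD.

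The t-test noncentrality is d × √(270 × 135/405) = d × 9.487, or 3.14 and 3.64.

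| Rates | Two-sided: binary → t-test | One-sided: binary → t-test |
|---|---|---|
| 48.6 vs 35.7 | 71% → 88% (+17) | 81% → 93% (+12) |
| 50.7 vs 35.7 | 83% → 95% (+12) | 90% → 98% (+8) |

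**5. Same shift, all controlled children tied at the floor.** A rank test was simulated. Two-sided power is about 82% (+11) and 91% (+8). One-sided, the gains are about 8 and 6 points. Allowing for simulation error, the range is about 5 to 11 points.

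**6. Treatment changes only the proportion controlled.** Here uncontrolled children have the same distribution in both arms. A tied-floor rank test, two-sided, has about 60% power against 71% for the binary test, and about 74% against 83%. The full-scale test loses about 10 to 11 points in this run. The loss depends on the shape assumed for uncontrolled children, and about 6 to 13 points is a fair range.

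**The case against.** The binary analysis is not arbitrary. The trial is sized on a control rate, the article defines clinical control and uses it as a decision point at week 12, and Table 4 heads its graded criteria as primary outcome. The logistic model therefore fits the sample-size basis better than the Outcomes section does. This stands. It means that the conflict could also be settled by changing the declared outcome.

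The group and time sentence reads like repeated-measures language, and the Outcomes section does promise to "compare the differences in urine protein between the two groups at each node". A reader might infer that the plan analyses nothing but cut-down versions of 24-h protein. The text does not support that: the sentence could be meant for the quantity, and the Cox outcome includes occult blood, so it is not purely a cut of 24-h protein. Still, the variable named in that sentence is curative effect, and no model is attached.

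Model detail such as transformation or a floor rule is commonly left to an analysis plan that is not shown. That is fair, and the point does not rest on it. It rests on the article assigning methods to other variables and none to its declared primary.

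**Conclusion.** The mismatch holds and does not depend on any power figure. Followed as written, the named models do not test the declared primary outcome on its own scale, and the sample size rests on a further version of it.

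A reader might also infer that dichotomising costs a definite amount of power at the plan's own rates. The documents do not support this, because they give no SD, distribution, normal limit or sidedness. At 270:135:

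- Under a uniform normal shift, the full-scale analysis gains about 12 to 17 points (two-sided 5%) or 8 to 12 points (one-sided 5%).
- With controlled children tied at the floor, it gains about 5 to 11 points.
- If only the proportion controlled changes, it loses about 6 to 13 points (two-sided 5%).

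Even the direction is therefore open. None of these figures includes baseline adjustment.

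**What to change.** In the Statistical analysis section, name one primary analysis that matches the Outcomes section: a repeated-measures model on (log) 24-h protein with arm, visit, arm-by-visit, the week-0 value and the light/heavy stratum. Read the arm difference at one pre-named week, and add a rank-based check for values at the floor. Keep the logistic model on clinical control, the type of outcome on which the sample size is based, as a key supportive analysis.

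Alternatively, restate the primary outcome in the Outcomes section as clinical control of proteinuria at one fixed week, and move the quantity to a supportive role.

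Either way, fix and date the choice before any comparison by arm. The trial is open-label and Trial status places it at the statistical stage, so a later change could look data-driven. No new data are needed. The small downside of the first option is an effect measure, such as a ratio of geometric means, that is less familiar to clinicians than a control rate. Reporting both deals with that.
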